### Secondary objectives

#### Epidemiological

To assess the effectiveness of ITWL + LLINs compared to LLINs alone, on time to first episode of malaria (asymptomatic and symptomatic) in children aged 6 months to 11 years old.To assess the effectiveness of ITWL + LLINs compared to LLINs alone, on mean haemoglobin concentration in children aged 6 to 59 months old.

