### Study endpoints

#### Epidemiological

Primary endpoint: the cumulative incidence of malaria parasitaemia (asymptomatic and symptomatic) defined as the number of mRDT-confirmed episodes of parasitaemia per child per year. A child will be considered to have experienced an episode of parasitaemia during a given month if they had a positive mRDT during the scheduled monthly follow-up visit, irrespective of symptoms. Two consecutive positive scheduled mRDT results will be treated as two separate episodes and any malaria cases diagnosed and treated at health facilities between monthly visits will also be counted as episodes.

Secondary endpoints: (i) time to first episode of malaria parasitaemia (asymptomatic and symptomatic) as determined by mRDT as per the primary case definition; (ii) changes in mean levels of haemoglobin among cohort children aged 6 to 59 months.

All study outcomes will be compared between the intervention (ITWL + LLINs) and the control arm (LLINs only).

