### Sample size rationale

#### Epidemiological

LLINs can reduce malaria morbidity by approximately 40–70 % [3]; the impact of ITWL alone or in combination with LLINs on malaria is unknown. The effects may be additive or synergistic (e.g. by having a mass killing effect and/or reducing mosquito longevity) or antagonistic (e.g. if the LLINs are repellent thereby reducing mosquito house entry and contact with ITWL). Due to the intensity and projected cost of the ITWL intervention, a minimum reduction in malaria of 30 % is considered of public health importance.

For the cohort study, sample size is based on annual cumulative incidence of malaria infection in each study arm as the primary outcome. From baseline surveys conducted in Muheza, it was assumed that cumulative incidence of malaria would be 2.5–3.0 detected episodes/year, with a coefficient of variation (CV) between clusters of 0.302 and an intra-cluster correlation (ICC) of 0.047. Therefore with 22 clusters per arm, sampling an average of 110 children (assuming 18 % loss to follow-up) per cluster, the study will have >85 % power to detect a 30 % reduction in malaria incidence at the 5 % significance level [59].

To measure time to first malaria episode during the evaluation year, assuming an ICC of 0.047, for a cumulative incidence of 2.0 episodes/year, the monthly risk would be 0.167. Using a binomial distribution calculation, the probability of having zero positive determinations (i.e. of ‘surviving’ malaria-free) over 1 year is (1–0.167)^12^ = 0.112; with a monthly 30 % reduction in risk, the cumulative probability of having no monthly positive RDTs in 12 months in the intervention arm would be (1–0.117)^12^ = 0.226. Sampling from 44 clusters with 90 children per cluster, the study will have 99 % power to reject the null hypothesis of no difference in ‘survival’.

To assess the effectiveness of the interventions on anaemia in children aged 6 to 59 months, assuming mean haemoglobin of 10.75 g/dl, 22 clusters in each study arm and a CV of 0.048, the study will be able to detect a difference of 0.5 g/dl in mean haemoglobin with 5 % significance and 85 % power between the study arms, sampling an average of 45 children per cluster.

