### Data analysis

All statistical analyses will be performed using STATA version 13 (StataCorp LP, College Station, TX, USA). The primary endpoint will be a comparison of the cumulative incidence of symptomatic or asymptomatic episodes of malaria in children between the two intervention groups. Data from cohort members who are lost to follow-up or who missed monthly visit(s) will be treated as censored. Similarly, children who are taking anti-malarial drugs, based on a positive mRDT, will be excluded in the analysis for the first 2 weeks following treatment. History of travel away from the study village will be recorded during monthly visits and time at risk will be censored for such periods. In addition, malaria cases in children who resided outside their cluster area for more than half of the elapsed study period at the time of illness will be excluded.

An initial analysis will compare the cumulative malaria incidence rates between the two study arms to assess the number of episodes of malaria parasitaemia (symptomatic, asymptomatic or combined) per child per year. A follow-up analysis will examine the time to first episode of clinical malaria. The rate ratio (RR) will be calculated by dividing the incidence rate in the intervention relative to the control arm. The effectiveness of ITWL + LLINs vs. LLINs alone will be obtained from the final analysis as 1-RR. Cox regression modeling will be used to investigate potential confounding such as season and age. A priori confounders will be included in the model and that the presence of effect modification or interaction terms will be explored. Both intention to treat (all persons randomized) and per protocol analyses (all persons who received the intervention) will be conducted. All analyses will be adjusted for within-cluster correlation using generalized estimating equations or random effects models with gamma frailty. In addition, missing data will be analyzed and multiple imputation used, if required.

Similarly, mean haemoglobin in 6–59 month olds will be measured and compared between the two arms.

Other outcome variables, including entomological indices, cost-effectiveness and acceptability of interventions will be compared between study arms accounting for any correlated observations within clusters or households.

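### The analysis section plans time to first clinical malaria, but the secondary objective, the endpoint and the power calculation are for first parasitaemia with or without symptoms

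*Protocol article*

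**What the plan says.** Four places in the protocol article describe the time-to-first-episode outcome.

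- **Secondary objectives, Epidemiological:** the effect of the wall lining plus nets "on time to first episode of malaria (asymptomatic and symptomatic) in children aged 6 months to 11 years old".
- **Study endpoints, Epidemiological, secondary endpoint (i):** "time to first episode of malaria parasitaemia (asymptomatic and symptomatic) as determined by mRDT as per the primary case definition". The primary case definition counts a child as having an episode in a given month "if they had a positive mRDT during the scheduled monthly follow-up visit, irrespective of symptoms". It also counts malaria diagnosed and treated at health facilities between visits.
- **Sample size rationale, Epidemiological:** "for a cumulative incidence of 2.0 episodes/year, the monthly risk would be 0.167". Then, "with a monthly 30 % reduction in risk", "the cumulative probability of having no monthly positive RDTs in 12 months in the intervention arm would be" 0.226, against 0.112 in the control arm. With 44 clusters of 90 children and an ICC of 0.047, the stated power is 99 %.
- **Data analysis:** "A follow-up analysis will examine the time to first episode of clinical malaria".

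The sentence just before the last one plans to compare episode rates for symptomatic episodes, asymptomatic episodes and the two combined. No symptom or fever criterion for clinical malaria appears anywhere in the article.

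**The concern.** The first three places agree on one event, a positive test regardless of symptoms. The fourth names another. An analyst who follows Data analysis literally would ignore every asymptomatic positive until a symptomatic episode occurred. The result would not answer the stated secondary objective.

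The mismatch leaves gaps on both sides. Secondary endpoint (i) has no time-to-event analysis assigned to it. First clinical malaria has an analysis but is not a listed endpoint, has no definition and was not considered in the sample size. While both versions stand, the choice of event is open and could be settled after the data are seen.

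**Working it through.** **1. Which event does each place use?**

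| Section | Event | Symptoms required? |
|---|---|---|
| Secondary objectives | first malaria episode | no, both kinds named |
| Study endpoints, secondary (i) | first mRDT-confirmed parasitaemia | no, primary case definition |
| Sample size rationale | first positive monthly RDT | no |
| Data analysis | first clinical malaria | yes by ordinary meaning; not defined |

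Data analysis itself separates symptomatic from asymptomatic episodes one sentence earlier, so the section does treat them as different. If clinical malaria means the symptomatic episodes among those that count under the primary definition, it is a subset and cannot be the more frequent event.

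**2. Does the stated 99 % reproduce for first parasitaemia?**

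Inputs from Sample size rationale: 2.0 episodes/year in the control arm, 30 % reduction in monthly risk, ICC 0.047, 22 clusters per arm, 90 children per cluster. The 5 % significance level is stated for the primary outcome; I take it as two-sided and the same here. The article does not give its power formula, so I use the usual comparison of two proportions with a design effect.

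- Event-free at 12 months: (1 − 2/12)^12 = 0.112 and (1 − 0.7 × 2/12)^12 = 0.226, as stated.
- Design effect: 1 + (90 − 1) × 0.047 = 5.183.
- Effective children per arm: 22 × 90 / 5.183 = 382.
- Standard error under the null (pooled proportion 0.169): √(2 × 0.169 × 0.831 / 382) = 0.0271.
- Standard error under the alternative: √((0.112 × 0.888 + 0.226 × 0.774) / 382) = 0.0268.
- Power: Φ((0.114 − 1.96 × 0.0271) / 0.0268) = Φ(2.27) = 98.8 %.

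An events-based (Schoenfeld) calculation with 636 effective events gives 99.4 % at a hazard ratio of 0.70. The 99 % is confirmed, for test positivity regardless of symptoms.

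**3. What would the same calculation give for first clinical malaria?**

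This needs the share of episodes that are symptomatic, which the article does not give. I assume a range and keep the 30 % reduction, the ICC and the 382 effective children per arm. The monthly risk becomes share × 2/12.

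| Assumed symptomatic share | Episodes/year | Event-free, control | Event-free, intervention | Power |
|---|---|---|---|---|
| 100 % | 2.0 | 0.112 | 0.226 | 98.8 % |
| 50 % | 1.0 | 0.352 | 0.486 | 96.5 % |
| 30 % | 0.6 | 0.540 | 0.652 | 88.4 % |
| 20 % | 0.4 | 0.666 | 0.753 | 76.0 % |

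Power falls below 80 % between a share of 25 % (83.4 %) and one of 20 %.

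**The case against.** **Loose wording.** The best defence is that this is one careless phrase in a condensed article. The Discussion also uses clinical malaria for the aim of the whole trial, although the primary endpoint is parasitaemia regardless of symptoms. The objective, endpoint and power text agree, so the intention is fairly clear. That makes a slip the likeliest explanation and limits the weight of the point. It does not remove the conflict: the outlying phrase sits in the section that says what will be analysed. A separate analysis plan would not cure it either, because the text shown contradicts itself.

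Three stronger readings are tempting, and the article does not support them.

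- **That the 99 % is wrong.** A reader may notice that this calculation uses 2.0 episodes/year, whereas for the primary outcome "it was assumed that cumulative incidence of malaria would be 2.5–3.0 detected episodes/year". But 2.0 is given openly as the condition of the calculation, and step 2 confirms the figure. At 2.5 and 3.0/year the same method gives 98.3 % and 96.7 %. An ICC of 0.065 in place of 0.047 (design effect 6.79, 292 effective children per arm) still gives about 96 %. Lower figures need a model of cluster risks and a cluster-level test that the article does not specify.
- **That the event would rest on fever recall in an unblinded trial.** Clinical malaria is not defined, and the examination at each follow-up visit includes temperature. A definition could use measured fever plus a positive test.
- **That the clinical malaria analysis would be underpowered.** That depends wholly on the symptomatic share. At 50 % the loss is about two points.

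**Conclusion.** The inconsistency is real and is confined to one secondary endpoint. Followed literally, Data analysis would test a narrower, undefined event and leave secondary endpoint (i) without its analysis. The stated 99 % holds for first parasitaemia and does not apply to first clinical malaria. For the latter, about 97 %, 88 % or 76 % are illustrations at assumed symptomatic shares of 50 %, 30 % and 20 %, with the same relative reduction and ICC. They are not estimates of what the trial would have. The primary endpoint, the sample size and the power figure for first parasitaemia are unaffected. The correction should be made because it settles which event is tested at almost no cost.

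**What to change.** In Data analysis, replace the reference to clinical malaria so that the follow-up analysis is of time to first malaria parasitaemia, asymptomatic or symptomatic, by the primary case definition. This matches secondary endpoint (i).

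If time to first clinical malaria is also wanted, give it a case definition and list it separately as exploratory, without attaching the 99 % to it.

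Leave the 99 % for first parasitaemia as it stands. The cost is one phrase, or one further definition if the extra outcome is kept. Nothing changes in the design, the sample size or the data collected.

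### The time-to-first-event analysis is written for clinical malaria, but the objective, secondary endpoint (i) and the 99 % power all concern first mRDT-positive parasitaemia with or without symptoms

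*Protocol article*

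**What the plan says.** Four places in the protocol article describe the time-to-first-event outcome in detail.

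- **Secondary objectives, Epidemiological:** the effect of wall lining plus nets "on time to first episode of malaria (asymptomatic and symptomatic) in children aged 6 months to 11 years old".
- **Study endpoints, Epidemiological, secondary endpoint (i):** "time to first episode of malaria parasitaemia (asymptomatic and symptomatic) as determined by mRDT as per the primary case definition". The primary case definition it refers to counts a child as having an episode in a given month "if they had a positive mRDT during the scheduled monthly follow-up visit, irrespective of symptoms", and adds cases diagnosed and treated at health facilities between visits.
- **Sample size rationale, Epidemiological:** power is worked out from "the cumulative probability of having no monthly positive RDTs in 12 months", so any positive test is an event.
- **Data analysis:** "A follow-up analysis will examine the time to first episode of clinical malaria".

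The first three agree with each other. The fourth names another event.

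**The concern.** A first positive mRDT and a first clinical episode are different events with different rates. A child who tests positive without symptoms has reached the first but not the second. An analyst who follows Data analysis to the letter would run a comparison that matches neither the declared endpoint nor the calculation behind its 99 % power.

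Two things are at stake. A reader could attach the 99 % to a result it was never calculated for. And with two candidate events in one document, the choice between them is less firmly fixed in advance than it should be. This matters somewhat more because Randomization and blinding says the lining cannot be installed blind, and classifying an episode as clinical would draw partly on the illness history given by parents or guardians.

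**Working it through.** **Step 1. Compare the event in each place.**

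| Section | Event | Symptoms required? |
|---|---|---|
| Secondary objectives | First malaria episode | No |
| Study endpoints, secondary (i) | First mRDT parasitaemia, primary case definition | No |
| Sample size rationale | First positive monthly test | No |
| Data analysis | First episode of clinical malaria | Yes, on its face |

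The sentence just before the one at issue in Data analysis distinguishes symptomatic, asymptomatic and combined episodes. The section draws the distinction and then names only the clinical event.

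**Step 2. Reproduce the stated power.** Inputs from Sample size rationale: "for a cumulative incidence of 2.0 episodes/year, the monthly risk would be 0.167"; a 30 % reduction, to 0.117; ICC 0.047; 44 clusters, so 22 per arm; 90 children per cluster. Assumed: two-sided 5 %. The article gives 5 % for the primary outcome and does not state sidedness.

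- Event-free at 12 months, control: "over 1 year is (1–0.167)^12^ = 0.112"; event proportion 1 − 0.112 = 0.888.
- Event-free, intervention: 0.226 as stated; event proportion 0.774. (Unrounded, (1 − 0.7/6)^12 = 0.2257, so the printed figure is right.)
- Design effect: 1 + (90 − 1) × 0.047 = 5.183.
- Effective number per arm: 22 × 90 / 5.183 = 382.
- Mean proportion: 0.831. Standard error under the null: √(2 × 0.831 × 0.169 / 382) = 0.0271. Under the alternative: √((0.888 × 0.112 + 0.774 × 0.226) / 382) = 0.0268.
- Power: Φ((0.114 − 1.96 × 0.0271) / 0.0268) = Φ(2.27) = 0.988.

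This agrees with the stated 99 %. A Schoenfeld calculation on effective events, with hazard ratio ln 0.226 / ln 0.112 = 0.679, gives 0.998. A cluster-level t calculation with 42 degrees of freedom gives 0.986. The figure is sound for first positivity with or without symptoms.

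**Step 3. Illustrate a symptomatic-only event.** The article does not give the share s of positives that are symptomatic, so s is an assumption. Monthly risks become 0.167s and 0.117s. The 30 % effect, the ICC and the numbers are held fixed, which is also an assumption.

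| s (assumed) | Event proportion, control | Event proportion, intervention | Power, two proportions | Power, Schoenfeld |
|---|---|---|---|---|
| 1.00 | 0.888 | 0.775 | 0.988 | 0.998 |
| 0.50 | 0.649 | 0.515 | 0.965 | 0.973 |
| 0.30 | 0.460 | 0.349 | 0.883 | 0.892 |
| 0.25 | 0.401 | 0.300 | 0.833 | 0.842 |
| 0.20 | 0.335 | 0.247 | 0.759 | 0.768 |
| 0.10 | 0.183 | 0.132 | 0.494 | 0.502 |

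Only the product of rate and share enters. The table uses 2.0 episodes per year, as the time-to-event calculation does; the primary outcome assumes 2.5 to 3.0. At 2.5, a 20 % share gives 2.5 × 0.20 = 0.5 clinical episodes per year, the same as the 25 % row (2.0 × 0.25). At 3.0, it gives 0.6, the same as the 30 % row.

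**The case against.** The strongest reply is that this is a slip of wording. The objective, the endpoint and the power basis are consistent; the abstract speaks only of time to first malaria episode; and Study endpoints says that all study outcomes will be compared between arms, which includes endpoint (i). The Discussion also describes the trial as testing protection against clinical malaria, although the primary endpoint counts infection irrespective of symptoms. The article thus uses the term loosely elsewhere.

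Much of this stands. A reader might infer that the declared endpoint has been dropped and replaced. One sentence does not show that, given the statement that all outcomes will be compared. A reader might also count the lack of a case definition for clinical malaria as a fault in itself. A fever threshold or recall window is commonly left to the full protocol or analysis plan, neither of which is shown, so no finding rests on it. The bias contrast is one of degree: temperature and an mRDT are taken at every monthly visit, and facility-diagnosed cases between visits already enter the parasitaemia definition, so that too depends partly on care seeking.

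The contradiction remains. Nothing in the article says that clinical malaria means any parasitaemia, and Data analysis itself separates symptomatic from asymptomatic infection one sentence earlier.

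**Conclusion.** The inconsistency is certain and must be reconciled: the event named for the time-to-first-episode analysis is not the event in the objective, in secondary endpoint (i) or in the power calculation.

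Its cost in power is not established. A reader might infer from the lower rows of the table that the trial is underpowered for this outcome. The documents do not support that: each lower figure depends on an assumed symptomatic share with the effect and ICC unchanged, and the loss is small if half or more of positives are symptomatic. What can be said is that the 99 % belongs to any mRDT-positive episode, and that power for a symptomatic-only event cannot be determined from the article. The primary incidence comparison, its definition and its power are unaffected.

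**What to change.** In Data analysis, replace the event in the follow-up sentence with time to first mRDT-confirmed parasitaemia, asymptomatic or symptomatic, as defined for secondary endpoint (i). The 99 % then applies as printed and nothing needs recalculating.

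If an analysis of clinical malaria is also intended, list it as a separate additional outcome and say that the 99 % does not apply to it.

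The cost is one sentence, or two if the additional outcome is kept. No change to design, sample size or data collection is needed. The correction should be made before analysis.

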**Methods/design:**

A two-arm cluster randomized controlled trial will be conducted in rural Tanzania to assess whether non-pyrethroid ITWL and UC of LLINs provide added protection against malaria infection in children, compared to UC of LLINs alone. Stratified randomization based on malaria prevalence will be used to select 22 village clusters per arm. All 44 clusters will receive LLINs and half will also have ITWL installed on interior house walls. Study children, aged 6 months to 11 years old, will be enrolled from each cluster and followed monthly to estimate cumulative incidence of malaria parasitaemia (primary endpoint), time to first malaria episode and prevalence of anaemia before and after intervention. Entomological inoculation rate will be estimated using indoor CDC light traps and outdoor tent traps followed by detection of *Anopheles gambiae* species, sporozoite infection, insecticide resistance and blood meal source. ITWL bioefficacy and durability will be monitored using WHO cone bioassays and household surveys, respectively. Social and cultural factors influencing community and household ITWL acceptability will be explored through focus-group discussions and in-depth interviews. Cost-effectiveness, compared between study arms, will be estimated per malaria case averted.

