### Randomization and blinding

In cluster randomized controlled trials it is particularly important to minimize imbalance for factors known to be highly correlated with disease outcome, in this case house construction/presence of open eaves and LLIN usage. Since all households will be provided with LLINs and the majority of homes have open eaves (89 % during baseline surveys), clusters will be stratified into two groups based solely on malaria prevalence; clusters in each stratum will then be randomly assigned to the two study arms. Stratified randomization of villages will reduce the likelihood of chance imbalances between study arms but as only a relatively small number of units can be randomized in such a cluster design, both groups cannot be assumed comparable for all factors. Baseline data on malaria prevalence and haemoglobin concentration collected from all enrolled cohort participants will be used to assess disparity in disease burden at the village level prior to study monitoring.

Observer bias will be reduced where feasible; because of the visible and obvious nature of the intervention, it is not possible to conduct ITWL installation in a blinded manner. Mosquito collector bias will be reduced by using standard CDC miniature light traps and Furvela tent traps, which do not rely on the technical ability of the fieldworker to collect specimens. Trap catches will be examined by a different person to the trap collector and they will be blinded to the trap location and intervention status. The intervention implementation, for both ITWL installation and LLIN distribution, will be monitored closely for quality and to document any bias between the clusters. Epidemiological data entry will be conducted using smartphones to minimize errors in collection; GPS location and time of questionnaire administration will also be recorded to ensure that interviews are appropriately conducted and adequate time has been devoted to data collection.

Loss to follow-up will be minimized through the use of community health workers (CHWs) from each cluster to ensure children are available during monthly study visits. In the event of missing participants, the study team, assisted by CHWs, will undertake home visits to locate cohort members or may extend the monthly visits to each cluster to sample participants who are temporarily unavailable. Extended periods of time spent living away from a participant’s cluster will be recorded and factored into the analysis.

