### Clinical evaluations and patient treatment

Incidence of malaria parasitaemia (asymptomatic or symptomatic) will be measured among the study cohort monthly for 1 year by teams, each consisting of an experienced nurse or clinical officer and a CHW. Following informed consent, at house-to-house enrollment, socio-demographic and economic information, including age, sex, education, sleeping habits, mosquito net use, household wealth, migration and health care-seeking behavior will be collected using a standardized questionnaire. The clinical team will initially assess each child for any severity signs and referrals will be made for those with severe criteria. Each child will then undergo a clinical assessment, including a full medical history and physical examination (weight, mid-arm circumference for children <5 years old, height, respiratory rate, pallor and temperature), and blood will be collected by finger-prick to perform an immediate mRDT among all cohort members and to measure haemoglobin concentration using a HemoCue® spectrophotometer (AB Leo Diagnostics, Helsinborg, Sweden) in those aged 6 to 59 months.

At enrollment, all children will receive a curative weight-appropriate three-day course of artemether-lumefantrine (ALU), according to the Tanzanian National Treatment Guidelines. Baseline treatment is intended to clear any parasitaemia, irrespective of symptoms, considering recent data suggest >50 % of malaria patients confirmed by PCR are asymptomatic and negative by mRDT or microscopy [42], and ALU provides a prophylactic effect, thus reducing the likelihood that a cohort member will acquire infection prior to the intervention. Adherence to the first ALU dose will be observed by the study team at enrollment and parents/guardians will be instructed to administer the subsequent doses. Regimen completion will be checked by CHWs and verified at the first month visit by production of the empty drug packet. Families whose children are enrolled will be issued an enumerated identify card containing participant number and village and the scheduled dates for subsequent visits.

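### Clusters are randomised within prevalence strata, but the stated analysis names neither the stratum nor cluster prevalence; if they are left out, intervals are too wide and the test is conservative

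*Protocol article*

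**What the plan says.** Under Randomization and blinding, "clusters will be stratified into two groups based solely on malaria prevalence", and "clusters in each stratum will then be randomly assigned to the two study arms". The abstract gives 22 clusters per arm. The same section warns that, with few units, the arms may still differ on some factors. It says that baseline prevalence and haemoglobin from the enrolled cohort "will be used to assess disparity in disease burden at the village level prior to study monitoring". Clinical evaluations and patient treatment describes the source of that cohort prevalence: at enrolment "blood will be collected by finger-prick to perform an immediate mRDT among all cohort members".

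Data analysis sets out the effect analysis. The rate ratio is the incidence rate in the intervention arm divided by that in the control arm. All analyses allow for within-cluster correlation, by generalised estimating equations or gamma-frailty random effects. On covariates it says "Cox regression modeling will be used to investigate potential confounding such as season and age", and adds that confounders chosen in advance will be in the model, without listing them. Neither the randomisation stratum nor cluster prevalence is mentioned, and neither is excluded.

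**The concern.** Stratifying forces the arms to be balanced on prevalence, so the rate ratio varies less over repeated randomisations than it would under simple randomisation. An analysis without the stratum leaves the between-stratum variance in the standard error, although the design has removed it from the estimate. The reported uncertainty is then larger than the true uncertainty.

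This matters because differences between clusters dominate the variance here, and prevalence is the one factor the investigators chose as the basis for stratification. The article calls the effect of the lining unknown and sets a 30% reduction as the smallest of public health importance. If the true effect is smaller, interval width decides whether the trial can exclude 30%.

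**Working it through.** **Inputs (Sample size rationale, Epidemiological).** The assumed incidence is 2.5 to 3.0 episodes per child per year. The spread between clusters is given in these words: "with a coefficient of variation (CV) between clusters of 0.302 and an intra-cluster correlation (ICC) of 0.047". The article plans 110 children per cluster with 18% loss, so 110 × 0.82 ≈ 90 child-years, and 22 clusters per arm. The target is a 30% reduction at the 5% level (two-sided assumed).

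**1. The plan's own power.** Use the usual formula for unmatched cluster rates: power = Φ(√[(c−1)(λ0−λ1)² / ((λ0+λ1)/y + k²(λ0²+λ1²))] − 1.96), with c = 22, λ0 = 2.5, λ1 = 1.75, y = 90, k = 0.302.
- Denominator: 4.25/90 + 0.0912 × 9.3125 = 0.0472 + 0.8493 = 0.8966.
- Root: √(21 × 0.5625 / 0.8966) = 3.63. Power = Φ(1.67) = 95.3%.
- At 3.0 episodes per year the result is 95.4%.
- The harshest variant takes the within-cluster variance from the ICC and gives both arms the control-arm variance. It yields 82.8% with c−1 and 84.5% with c.

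The stated figure is therefore reproduced without any adjustment for stratum.

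**2. Where the variance lies.** Per cluster, on the log-rate scale, the between-cluster part is 0.302² = 0.0912 and the Poisson part is 1/(90 × 2.5) = 0.0044. The total is 0.0956, of which about 95% is between clusters.

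**3. Effect of leaving out the stratum.** Assume two equal strata split at the median and approximate normality. The split then removes (2/π)ρ² = 0.637ρ² of the between-cluster part. With q = (0.0956 − 0.637ρ² × 0.0912)/0.0956, actual type I error = 2[1 − Φ(1.96/√q)].

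| Assumed rho | q | Type I, formula | Type I, simulation without stratum | Type I, simulation with stratum |
|---|---|---|---|---|
| 0 | 1.000 | 5.0% | 4.95% | 4.9% |
| 0.3 | 0.945 | 4.4% | 4.4% | 4.9% |
| 0.5 | 0.848 | 3.3% | 3.3% | 4.9% |
| 0.7 | 0.703 | 1.9% | 2.2% | 5.2% |

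The simulation drew 44 cluster log-rates in two strata of 22, allocated 11:11 within each, with 20,000 runs under no effect. At rho 0.5 the mean reported standard error without the stratum was 0.0913 against a true SD of 0.0845 (8% too wide). At rho 0.7 it was 0.0916 against 0.0778 (18%).

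**4. Sensitivity to the within-cluster variance.** The ICC implies a total variance of (0.302 × 2.5)²/0.047 = 12.13. The within-cluster term is then (12.13 − 0.57)/(90 × 2.5²) = 0.0205 instead of 0.0044. The formula gives 4.5%, 3.6% and 2.3% at rho 0.3, 0.5 and 0.7, so the pattern is the same.

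**5. What adjustment buys.** With equal allocation within strata, the stratum term corrects the reported standard error but leaves the true spread of the estimate as it was. Cluster prevalence as a continuous term reduces that spread too. If it explains ρ² of the between-cluster variance, the standard error is multiplied by √[(0.0912(1−ρ²) + 0.0044)/0.0956]. At rho 0.5 this is 0.873, a fall of 13%.

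Simulated power (8,000 runs), unadjusted / stratum / stratum plus prevalence:

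| Assumed rho | 30% reduction | 20% reduction |
|---|---|---|
| 0.5 | 97 / 98 / 99% | 67 / 73 / 76% |
| 0.7 | 98 / 99 / 100% | 69 / 81 / 89% |

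**The case against.** The strongest reply is that a journal article need not list model covariates. Season and age are given as examples, other confounders are to be fixed in advance, and the only stratification factor is an obvious candidate for that list. Using cohort prevalence to look for disparity does not rule out adjusting for it. Much of this stands: the article does not show that stratum and prevalence will be left out, only that they are not named. What remains is that Data analysis does state the effect measure, the clustering method and example covariates, and passes over the one factor that defined the randomisation.

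A reader might also infer that the analysis is invalid, inflates false positives, biases the rate ratio or leaves the trial underpowered. The article supports none of these. The error runs in the safe direction, the ratio is unbiased, and at the design effect the loss is at most about 2 points of power. The larger losses (9 points at rho 0.5, 20 at rho 0.7) arise for a 20% reduction, which is below the article's own threshold of importance.

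Finally, a reader might reach for the enrolment mRDT prevalence as a ready covariate. Study intervention implementation has lining installation starting in all buffer areas. In each intervention cluster, cohort enrolment precedes installation in the core, but it may follow installation in the buffer. A value that may already reflect treatment could absorb part of the effect.

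**Conclusion.** The point holds as a gap between the stated design and the stated analysis that costs little to close. If stratum and prevalence are omitted, the test runs at about 4.4%, 3.3% or 2% instead of 5% for rho 0.3, 0.5 or 0.7, and reported standard errors are about 8% too wide at rho 0.5 and 18% at rho 0.7. At rho 0 there is no effect. These figures rest on an assumed rho, on equal strata split at the median, and on 0.302 being the overall coefficient of variation. The article does not say whether 0.302 is overall or within strata. If it is within strata, an unadjusted analysis would face more variation than was planned for. Power for the 30% target does not depend on this point.

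**What to change.** In Data analysis, state that two models include the randomisation stratum as a prespecified fixed covariate: the primary count model (child-time offset, clustering accounted for) and the time-to-first-episode model. Preferably add the cluster prevalence that was used to form the strata, which by construction precedes randomisation. Report the ratio without these terms as supportive. Do not use enrolment mRDT prevalence unless it is shown to precede any installation of the lining in that cluster, buffer included.

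The cost is one or two sentences and one or two cluster-level degrees of freedom: 44 − 2 = 42 falls to 41 with the stratum and to 40 with prevalence as well. No new data are needed. If prevalence turns out to predict nothing, the loss is negligible: at rho 0 and a 30% reduction, simulated power is 96.6% unadjusted and 96.1% with both terms.
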